#### Run-in

Subjects with vitamin-D deficiency who are volunteering to participate in the study will be entered into the 2-week maintenance weight program after the above steps have been taken. Subjects will be asked not to change their lifestyle and keep researchers informed of any changes including diet, physical activity, and medicine use. At the end of the first visit, a pamphlet will be given to the individuals, containing the description of the study, the description of the food groups, a date for the next visit, and the contact number. The presence of this run-in period is needed for maintening their weight, as well as to test the participants’ motivation to continue the intervention.

#### Randomization/blinding

Those participants with vitamin- deficiency (< 50 nmol/L) will be randomly assigned to receive either vitamin-D-fortified breads or plain bread. Randomization will be done using a computer-based random-digit generator. The allocation will be done in a 1:1:1 ratio. The research team, all participants, the staff involved in the clinical center, and those assessing the outcomes and analyzing the data will be blinded to group assignment. Letter codes A, B, and C wil be used to identify the three groups, respectively. Breads will be packaged in identical color, size, and taste. Therefore, neither the participants nor the researchers, the interviewers or laboratory staff know which participants belong to which group,

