#### Participant recruitment

In this trial, we will recruit a total of 90 participants (each group 30 subjects) from apparently healthy subjects of Tehran, the capital city of Iran. Participant recruitment was expected to commence by September 2018, and the trial is due to last 20 months. This assumes 4 months for participants recruitment, 4 months for run-in periods and intervention, 2 months for laboratory testing, 2 months for data collection, preparing and entering into SPSS software, 3 months for data retrieval and analysis, and 4 months to write the study report. A Standard Protocol Items: Recommendations for Interventional Trials (SPIRIT) Checklist [32] was used to report this protocol (Additional file 1, SPIRIT Checklist). Table 1 also shows the trial schedule. Before collecting any information, informed consent will be obtained from all participants. After reviewing the consent forms and answering any probable questions by study staff, those who are interested will be asked to sign the forms. A copy of the consent form will be gave to participants and all original signed consent forms will be kept by the study staff (Additional file 2, consent form).

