#### Intervention

Breads will be either plain (PB; containing no vitamin D/100 g bread) or fortified with two different dosages of vitamin D3 (FB; containing 500 IU vitamin D3/100 g bread or containing 1000 IU vitamin D3/100 g bread). Participants will receive a package of bread for both lunch and dinner. The timeframe for the intervention will be 12 weeks. Consumption of 1000 IU/day vitamin D is believed to be safe and effective to increase circulating 25(OH) D levels [34]. Participants will be given packages of bread for 2 weeks. All subjects will be visited biweekly to both assess their compliance and provide them with bread packages for the next 2 weeks.

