#### Compliance

Participants will be asked to mark a reminder note for the daily consumption of bread. They will be given a sheet of paper that includes the code, the next visit date, two columns entitled “Lunch and dinner meals,” and another column entitled “Date” to record their regular consumption of bread. Patients will beinstructed to attach the sheet on the refrigerator in order to remind them of their use of the bread. Volunteers will return the sheet every 2 weeks and they will be provided with a new, 2-week, bread package.

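### One letter code per arm lets a single decoded letter reveal the treatment of a whole arm of 30; participant- or pack-specific codes would limit it to one person

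*Protocol article*

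**What the plan says.** The Randomization/blinding section of the protocol article sets the coding scheme: "Letter codes A, B, and C wil be used to identify the three groups". The same section fixes equal arms ("The allocation will be done in a 1:1:1 ratio"), and Participant recruitment gives their size: "we will recruit a total of 90 participants (each group 30 subjects". Blinding is meant to cover the research team, participants and clinic staff, and also "those assessing the outcomes and analyzing the data will be blinded to group assignment". The section then describes breads that cannot be told apart and concludes from this that participants, researchers, interviewers and laboratory staff do not know who is in which group.

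Two other sections bear on who handles coded material. Intervention says: "All subjects will be visited biweekly to both assess their compliance and provide them with bread packages for the next 2 weeks". Compliance says of participants: "They will be given a sheet of paper that includes the code, the next visit date". It does not say whether that code is the group letter or a participant number. No participant-specific or pack-specific code is described anywhere in the article.

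**The concern.** Identical bread hides the product. It does not hide a code that all members of an arm share. Where the letter is visible, staff and participants can see who belongs together, and only the meaning of three symbols remains hidden. Learning that meaning for one participant gives it for everyone with the same letter.

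The article itself describes situations in which questions about a letter could arise. Volunteers learn their vitamin D status at screening (Setting). Adverse events are recorded, and participants with abnormal samples are referred to a physician (Safety procedures). Recruitment is planned over 4 months (Participant recruitment) or 6 months (Trial status), against a 12-week intervention, so some participants can finish while others are still being enrolled. A letter decoded at that stage also applies to those who are given it later.

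At stake are the parts of the trial that depend on behaviour or self-report: the consumption sheet, dietary recall, the sun-exposure questionnaire, retention, and use of vitamin D from outside the trial. The last of these, and sun exposure itself, can change 25(OH)D. Laboratory measurement therefore does not fully protect the primary comparison if people learn their arm. Analyst blinding is exposed as well if the same letter is used in the field and in the dataset.

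**Working it through.** **Inputs.** 90 participants in total and 30 per group (Participant recruitment); 1:1:1 allocation and three letters for three groups (Randomization/blinding).

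**Participants per letter.** 90 / 3 = 30. This agrees with the arm size given in the Abstract, Participant recruitment and Sample size. The power calculation behind 30 cannot be repeated because the article gives no standard deviation, but nothing here depends on it.

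**One letter decoded, one letter per arm.**
- Revealed at full enrolment: 30 of 90.
- The other 90 − 30 = 60 participants are narrowed from three possible arms to two.
- During recruitment, about one third of those enrolled so far are revealed, for example 45 / 3 = 15 of 45. People who receive that letter later fill up the same 30; they do not add to it.

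**Two participants unblinded, one letter per arm.** If they are in different arms, two letters are known, the third follows by elimination, and all 90 are revealed. If they are in the same arm, the second break adds nothing. For two participants chosen at random:
- P(different arms) = 60/89 = 0.674
- P(same arm) = 29/89 = 0.326
- Expected number revealed = 0.326 × 30 + 0.674 × 90 ≈ 70.4 of 90

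**Other coding schemes.**

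| Scheme | Participants per code | Revealed by one break |
|---|---|---|
| One letter per arm (as stated) | 90/3 = 30 | 30 of 90 |
| Three codes per arm | 30/3 = 10 | 10 of 90 |
| Unique participant code | 1 | 1 of 90 |

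These figures describe how far a break spreads once it has happened. They do not say how likely a break is, and the article gives nothing from which to estimate that.

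**The case against.** The strongest reply is that the article never says the letter is printed on the packs or seen by the staff who hand out bread. The letters could be masked group labels for the dataset, which is a sound use of them. The code on the consumption sheet could be a participant number, which a sheet returned every two weeks would need anyway. The section also ends by saying that staff do not know the groupings. A condensed article may leave labelling and custody of the key to the full protocol.

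Part of this stands: visibility of the letters is an inference. It is nevertheless the natural reading. The letters are introduced within the blinding description, directly before the packaging, and the blinding conclusion is drawn from the two together. The point also does not rest on something left out, because the arm-level code is what the article states.

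Four stronger readings are tempting and are not supported:
- **Allocation concealment fails.** A reader might infer that a decoded letter tells recruiters what the next participant will get. That requires the upcoming letter to be visible. The article describes a computer-generated random allocation and no packs laid out in sequence.
- **Any two breaks open the whole trial.** This holds only if they fall in different arms, which for two random participants happens about two times in three.
- **The number of hand-overs measures the risk.** 90 participants × (12 weeks / 2 weeks) = 540 hand-overs, but a hand-over is not an unblinding, and no probability attaches to it.
- **The primary outcome is directly compromised.** 25(OH)D is measured by HPLC, which leaves little room for assessor bias. The remaining route is changed behaviour.

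It is also fair to say that one outside 25(OH)D result would not reliably decode a letter. Assuming a standard two-sample normal calculation, 30 per arm for a difference of 20 nmol/L at two-sided alpha 0.05 and 80% power implies SD = 20 × √(30/2) / (1.960 + 0.842) ≈ 27.6 nmol/L. The target difference is then smaller than one standard deviation (20/27.6 ≈ 0.72).

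**Conclusion.** The point holds as a weakness in the stated coding scheme that is cheap to remove. One letter per arm lets a single decoded letter reveal 30 of 90 treatments at full enrolment and narrow the other 60 to two arms, against 1 of 90 with unique participant codes. Breaks in two different arms reveal everyone.

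This rests on the letters serving as the working treatment code, visible to at least some of those who are meant to be blind. The text supports that reading but does not state it. The consequence lies mainly in compliance records, dietary and sun-exposure reporting, retention, outside vitamin D use and analyst blinding, and less in the measurement of 25(OH)D. The documents do not show that blinding has failed, that allocation is predictable, or how probable a code break is.

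**What to change.** In Randomization/blinding, state that each pack carries a unique participant or pack number taken from a list held by someone outside the research team. If that is impractical, use several codes per arm. State that masked letters A, B and C are given only to the analyst and do not appear on any material used in the field.

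In Compliance, state that the sheet carries only the participant number.

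If the full protocol already uses individual codes, one clarifying sentence in each of the two sections settles the matter. If bread has already been handed out under the letters, the trial report should say who could see them and whether any letter became known.

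The cost is label printing, a dispensing list and slightly more packing and dispensing work. Bread, visits, measurements and sample size do not change.

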#### Intervention

Breads will be either plain (PB; containing no vitamin D/100 g bread) or fortified with two different dosages of vitamin D3 (FB; containing 500 IU vitamin D3/100 g bread or containing 1000 IU vitamin D3/100 g bread). Participants will receive a package of bread for both lunch and dinner. The timeframe for the intervention will be 12 weeks. Consumption of 1000 IU/day vitamin D is believed to be safe and effective to increase circulating 25(OH) D levels [34]. Participants will be given packages of bread for 2 weeks. All subjects will be visited biweekly to both assess their compliance and provide them with bread packages for the next 2 weeks.

#### Compliance

Participants will be asked to mark a reminder note for the daily consumption of bread. They will be given a sheet of paper that includes the code, the next visit date, two columns entitled “Lunch and dinner meals,” and another column entitled “Date” to record their regular consumption of bread. Patients will beinstructed to attach the sheet on the refrigerator in order to remind them of their use of the bread. Volunteers will return the sheet every 2 weeks and they will be provided with a new, 2-week, bread package.

#### Patient and Public Involvement

There is no involvement of patients or public in this study.

### Outcome measurements

#### Dietary assessment

A 3-day 24-h dietary recall questionnaire will be used to evaluate vitamin D and calcium intake. It includesd two work days and one weekend. Then, the data from questionnaire will be analyzed using N4 software (NUTRITIONIST 4, First Data Bank, San Bruno, CA, USA).

#### Anthropometry measures

The height will be measured without shoes by a stadiometer (Seca, Germany) with a sensitivity of 0.1 cm and weight with a digital scale (808 Seca, Germany) while wearing light clothes (with no coat or raincoat) with a sensitivity of 0.1 kg. Body mass index (BMI) will be calculated by dividing the weight (in kilograms) by height squared (in meters). The waist circumference will be measured by a strip tape midway between the lowest rib and the iliac crest and during expiration. Then the waist to hip ratio (WHR) will be calculated for each person.

#### Blood pressure

Blood pressure (BP) will be measured twice for each person using a digital barometer (BC 08, Beurer, Germany) after at least 10–15 min of resting in a sitting position. Then, the average BP for each person will be calculated and recorded.

#### Body composition analysis

Body fat mass and visceral fat percentage will be measured by bioelectrical impedance analysis (Quadscan 4000 system, Bodystat, UK).

### Laboratory investigations

#### Blood collecting

A 20-mL blood sample will be taken in a fasting state between 7:30 and 9:00 and stored in an acid-washed tube without anticoagulant. Then, after being stored at room temperature for 30 min and following blood clot formation, centrifugation at a speed of 1500 g for 20 min will be carried out. After that, the serum will be collected into separate micro-tubes and stored in a freezer at − 80 °C freezer until laboratory analysis.

#### Blood cell count

A complete cell blood count (CBC) will be measured by a blood-cell counter (Mythic, Orphee, France).

#### Blood chemistry

Fasting blood sugar (FBS) and lipid profile (total cholesterol, low-density lipoprotein cholesterol (LDL-C), high-density lipoprotein cholesterol (HDL-C), and triglycerides (TG)) will be measured by enzymatic methods based on colorimetry using commercial kits (Pars Test, Iran) using the automatic device (Selecta E, Vitalab, The Netherlands). Alanine aminotransferase (ALT) and aspartate aminotransferase (AST) will be also be measured in the serum by enzymatic assays. Measurement of serum concentrations of albumin, calcium, phosphorus, and magnesiumwill be performed based on colorimetric method, using commercial kits (Pars Test, Iran) and an automatic device (Selecta E, Vitalab, The Netherland). These tests will be performed for all patients on the same day of blood sampling.

The serum level of 25(OH) D will be measured by high-performance liquid chromatography (HPLC). Serum intact parthyroid hormone (iPTH) level will be measured using commercial kits DRG ([name]) and using the enzyme-linked immunosorbent assay (ELISA) method.

#### Urinary tests

Calcium, phosphorus, magnesium, and creatinine will be measured using the colorimetric method, and microalbumin by the immunoturbidometric method using commercial kits (Pars Test, Iran) and automatic devices (Selecta E, Vitalab, The Netherland).

#### PBMC culture

Peripheral blood mononuclear cells (PBMCs) were separated using Ficoll-hypaque gradient density centrifugation and cultured as described elsewhere [30], with minor modifications. In this study, ~ 106 cells will be transferred to a culture well in a six-well cell-culture plate (Greiner bio-one, Germany), each well containing 1% phytohemmaglutinin (PHA) (Gibco), 100 ng/mL LPSs (Gibco, United States), 100 U/mL penicillin G and 10 ng/mL streptomycin (both from Sigma-Aldrich, United States) in a total volume of 2 mL RPMI 1640. PBMC culture is performed in triplicate.

#### Cytokine assay

Measuring the cytokines (serum highly sensitive C-reactive protein (hs-CRP) concentration, interleukin 4 (IL-4), interleukin 6 (IL-6), interleukin 10 (IL-10), tumor necrosis factor-α (TNF-α), and interferon gamma (INF-γ)) will becarried out in the culture medium.

#### Microbiota composition

The stool sample will be collected at baseline and at the end of the intervention and 16S ribosomal RNA (*16S rRNA*) genes, sequenced using polymerase chain reaction (PCR), will be applied to determine intestinal microbiome genome.

#### Gut permeability evaluation

Serum zonulin will be measured by ELISA. Serum LPSs will be measured using the HEK-Blue LPS Detection Kit (Invivogen, San Diego, CA, USA).

#### Safety procedures

We will record and report all adverse events, and participants with abnormal research samples will be referred to a physician.

### Statistical analyses

Data analysis will be done using SPSS version 21 software. To describe the quantitative data, the mean and standard deviations will be used and to describe the qualitative data absolute and relative abundance will be used. To compare absolute or relative abundance the chi-square or Fisher’s exact statistics will be used. As the data should compare groups, between groups, and between-group changes, and to reduce the probability of the error, an analysis of two-way variance with repeated measures will be used to explore the impact of time and time-group effects with adjustment using the Bonferroni post-hoc test. The effects of the intervention in each group were examined using the paired *t* test versus the baseline values. Between-group comparisons were examined using analysis of variance (ANOVA) followed by a Bonferroni post-hoc analysis. Covariance analysis will be used to adjust the effects of confounding variables. The correlation between the three groups will be evaluated by Pearson (normal data distribution) or Spearman (abnormal distribution). The significance level in this study will be considered to be *p* < 0.05.

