**Methods/design:**

A double-blind, randomized controlled clinical trial is conducted on apparently healthy individuals with vitamin-D deficiency. The random allocation is done to divide participants into intervention groups including daily intake of vitamin-D-3-fortified bread (FB) with 500 IU/100 g bread (*n* = 30), FB with 1000 IU/100 g bread (*n* = 30), and 100 g plain bread (PD) (*n* = 30). At baseline and after 3 months of the intervention period, blood, stool, and urine samples are taken. Anthropometric measures, body composition, blood pressure, and dietary assessment are made. The gut microbiome composition is measured by the 16S rRNA approach. Data is analyzed by SPSS software version 21.

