#### Sample size

Based on data on serum 25(OH) D changes from Nikooyehet al [33]., to achieve 20 nmol/L difference in circulating 25(OH) D with a two-sided alpha of 0.05 and a beta of 0.2 after a 12-week intervention period, the target sample size will be 30 individuals per treatment group. We are not adjusting the primary outcome comparisons for the multiple pairwise comparison.

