### Discussion

In the last decade, attention has widened to the intestinal microbiota as an overlooked system. The various roles of vitamin D in health and many of its receptors in every organ of the body, particularly the gut, has increased the probable role of the intestinal microbiota through vitamin-D-dependent pathways in health and disease. Therefore, vitamin-D deficiency seems to play a vital role in health due to its effect on this intestinal microbiota. Solving the vitamin-D-deficiency problem through fortification of foods is an efficient and economical solution. Fortification has long been considered as an optional and mandatory way to improve nutrient deficiencies in developed countries. Bread has a special place in the Iranian diet. It is a staple food eaten with every meal and is also economically accessible to all people in the community. Moreover, it is important to note that milk, which is frequently fortified in developed countries, is not a good carrier for fortification in Iran due to its low consumption by the Iranian people. This study was designed following two important goals; the first is the efficiency of vitamin-D-fortified bread in improving serum levels of vitamin D and the second one is to determine the effect of vitamin D on body composition, metabolic and inflammatory biomarkers, and gut microbiota in apparently healthy adults.

The current protocol has some strength including the randomized placebo-controlled clinical trial design that is the strongest empirical evidence of a treatment’s efficacy and suitable for causal inferences. The second strength is the fortification of bread in two doses, which can more accurately reflect the treatment effects. Determining the role of vitamin D and intestinal microbiota also takes place for the first time in this study and can be considered as the third strongest point of this protocol. One of the limitations of this protocol is the inability to measure the total microbiota profile of the intestine due to lack of funding. In addition, our study is a short-term study and requires more pilot studies to be carried out for community-based fortification. Moreover, our protocol is based on apparently healthy people and cannot be generalized to the patient’s community.

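### The microbiota outcome is described in ways that do not fit together, and the study-wide p < 0.05 rule does not control false positives across taxa

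*Protocol article*

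**What the plan says.** **Measurement.** The Abstract (Methods/design) states "The gut microbiome composition is measured by the 16S rRNA approach". Under Laboratory investigations, Microbiota composition, stool is collected at baseline and at the end of the intervention, and 16S rRNA genes, "sequenced using polymerase chain reaction (PCR), will be applied to determine intestinal microbiome genome". The Discussion lists as a limitation "the inability to measure the total microbiota profile of the intestine due to lack of funding".

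**Role.** Gut microbiota is in the title and the secondary objectives. The second hypothesis expects the fortified bread to improve it. The Discussion counts the microbiota work as the protocol's third strength.

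**Analysis.** The section Statistical analyses does not mention microbiota or taxa. Its general rules are:
- two-way repeated-measures analysis of variance with Bonferroni post-hoc tests
- paired t tests against baseline in each group
- ANOVA between groups, followed by Bonferroni
- covariance analysis for confounders
- Pearson or Spearman correlation
- one significance level, p < 0.05, for the study

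Qualitative data are described by absolute and relative *abundance*. The next sentence begins "To compare absolute or relative abundance the chi-square or" and goes on to name Fisher's exact test.

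**The concern.** There are two problems.

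First, a reader cannot tell what the outcome is. It could be a community profile by 16S sequencing or a limited set of targets by PCR. A claim about composition cannot rest on a profile that the protocol says it cannot measure.

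Second, microbiota data normally yield several taxa, and the only written error rule is p < 0.05 for the study. Bonferroni is attached to comparisons that follow an ANOVA, so it works within one variable and not across variables. The objectives also include within-group change, which adds three paired t tests per taxon. One or two chance taxa could then be reported as an effect of vitamin D on the microbiota.

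**Working it through.** **What the document gives.** There is no error rate, power or effect size for microbiota. The only sample-size figure concerns the primary outcome: "to achieve 20 nmol/L difference in circulating 25(OH) D", "with a two-sided alpha of 0.05 and a beta of 0.2 after a 12-week intervention period", with 30 per group. The standard deviation is not stated. Thirty per group corresponds to about 27.6 nmol/L, since 2 × 27.6² × (1.96 + 0.84)² / 20² ≈ 30. This cannot be checked and does not bear on the present point.

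**Step 1: the descriptions side by side.** The Abstract promises composition. The laboratory section promises the microbiome genome, although one marker gene is not a genome and PCR amplifies rather than sequences. The Discussion says the total profile is out of reach. The three can be reconciled only if the measurement is limited in scope, and neither the objective nor the hypothesis says so.

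**Step 2: error across taxa.** Inputs are a level of 0.05 (Statistical analyses), three arms (Randomization/blinding), and an assumed number of taxa m between 5 and 50. Taxa are taken as independent, with no true effect or change.
- One overall between-arm test per taxon: 1 − 0.95^m.
- Bonferroni over the three arm pairs only, pairs treated as independent: 1 − (1 − 0.05/3)^(3m).
- Paired t tests in three arms: 1 − 0.95^(3m).

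| Taxa (assumed) | Expected false positives, overall test (0.05m) | At least one, overall test | At least one, Bonferroni over arm pairs | At least one, paired t tests |
|---|---|---|---|---|
| 5 | 0.25 | 22.6% | 22.3% | 53.7% |
| 10 | 0.5 | 40.1% | 39.6% | 78.5% |
| 20 | 1.0 | 64.2% | 63.5% | 95.4% |
| 50 | 2.5 | 92.3% | 92.0% | 99.95% |

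The overall-test figure passes 50% at 14 taxa, since ln 0.5 / ln 0.95 = 13.5. Bonferroni over arm pairs barely changes the result because it does not span taxa.

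**Step 3: is ANOVA itself at fault?** A null simulation used 3 × 30 participants, beta-binomial taxon proportions with means of 1%, 5% and 20%, an assumed 10,000 reads per sample and 2,000 runs per setting. One-way ANOVA on per-participant proportions rejected in 3.7% to 5.1% of runs and Kruskal–Wallis in 4.0% to 5.9%. The level of a single test is therefore sound, and the fault lies in the number of tests.

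**The case against.** **A journal article condenses the full protocol.** Taxon lists, transformations, global tests and multiplicity for secondary outcomes are commonly left to an analysis plan that is not shown. This stands, and their absence is not held against the plan. What remains is what the article does state: one threshold for the study, within-arm paired tests, and Bonferroni only post hoc.

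**The descriptions may be compatible.** A 16S approach can be limited in scope, so composition by 16S and no total profile can both be true. This stands in part. The limitation is openly disclosed, but the objective, the hypothesis and the Abstract are not narrowed to match it.

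**The number of taxa is not in the document.** The stated limitation may even point to few targets, where the inflation is smaller. For one given arm contrast at the Bonferroni level of 0.05/3, the chance of a false positive somewhere among the taxa is 1 − (1 − 0.05/3)^m: 8.1% for 5, 15.5% for 10, 28.5% for 20 and 56.8% for 50. This stands as a limit on size.

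**A stronger reading is tempting.** A reader might infer from the word *abundance* that taxon data will be compared by chi-square on pooled sequence reads, which would count reads as if they were independent subjects. The document does not support that. The preceding sentence ties the word to qualitative data, nothing says that reads are pooled, and frequency is the natural meaning. Chi-square on per-participant presence or absence of a taxon kept its level in simulation (3.7% to 5.0%).

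**Conclusion.** The point holds in two parts. The descriptions of the microbiota measurement do not fit together and must be reconciled. The stated error rule, if applied to several taxa, does not control false positives across them: 23% at 5 taxa, rising to 92% at 50, for one overall test per taxon. These figures assume the number of taxa, independence and a complete null; correlation between taxa lowers them. Relying on within-arm paired t tests makes matters worse, both through the number of tests and because a change shared by all arms is not an effect of vitamin D.

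The document does not show that its methods are invalid for a single taxon, or that false claims are likely, because that depends on a number of taxa it does not give. The ambiguous word *abundance* is a clerical matter worth one edit.

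**What to change.** 1. Reconcile the Abstract, Microbiota composition and the Discussion. State one measurement, and limit the microbiota objective, hypothesis and conclusion to what it covers.
2. Analyse each taxon with the participant as the unit: ANCOVA of (log) end-of-study abundance on arm and baseline abundance. The baseline stool sample is already planned, and covariance analysis is already among the stated methods.
3. Base claims on between-arm contrasts with Benjamini–Hochberg control of the false discovery rate at 5% across taxa, and state the family. Do not base claims on within-arm paired t tests at p < 0.05.
4. In Statistical analyses, replace *abundance* by *frequency* for categorical variables, so that chi-square and Fisher's exact test are not applied to taxon data.

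**Cost.** Wording and a little more analysis, with no new data. Single-taxon claims become harder: with m tests in the family, a lone taxon must reach 0.05/m, for example 0.01 with 5 taxa or 0.0025 with 20. The requirement is milder when several taxa respond together.
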